# Enhancing LPG adoption in Ghana (ELAG): a factorial cluster-randomized controlled trial to Enhance LPG Adoption & Sustained use

**DOI:** 10.1186/s12889-018-5622-3

**Published:** 2018-06-04

**Keywords:** Clean cookstoves, Household air pollution, Sustained use, Clean cookstove adoption, Behavioral intervention, Structural intervention, Biomass combustion

## Abstract

**Background:**

Three billion individuals worldwide rely on biomass fuel [dung, wood, crops] for cooking and heating. Further, health conditions resulting from household air pollution (HAP) are responsible for approximately 3.9 million premature deaths each year. Though transition away from traditional biomass stoves is projected curb the health effects of HAP by mitigating exposure, the benefits of newer clean cookstove technologies can only be fully realized if use of these new stoves is exclusive and sustained. However, the conditions under which individuals adopt and sustain use of clean cookstoves is not well understood.

**Methods:**

The Enhancing LPG Adoption in Ghana (ELAG) study is a cluster-randomized controlled trial employing a factorial intervention design. The first component is a behavior change intervention based on the Risks, Attitudes, Norms, Abilities, and Self-regulation (RANAS) model. This intervention seeks to align these five behavioral factors with clean cookstove adoption and sustained use. A second intervention is access-related and will improve LPG availability by offering a direct-delivery refueling service. These two interventions will be integrated via a factorial design whereby 27 communities are assigned to one of the following: the control arm, the educational intervention, the delivery, or a combined intervention. Intervention allocation is determined by a covariate-constrained randomization approach. After intervention, approximately 900 households’ individual fuel use is tracked for 12 months via iButton stove use monitors. Analysis will include hierarchical linear models used to compare intervention households’ fuel use to control households.

**Discussion:**

Literature to-date demonstrates that recipients of improved cookstoves rarely completely adopt the new technology. Instead, they often practice partial adoption (fuel stacking). Consequently, interventions are needed to influence adoption patterns and simultaneously to understand drivers of fuel adoption. Ensuring uptake, adoption, and sustained use of improved cookstove technologies can then lead to HAP-reductions and consequent improvements in public health.

**Trial registration:**

NCT03352830 (November 24, 2017).

**Electronic supplementary material:**

The online version of this article (10.1186/s12889-018-5622-3) contains supplementary material, which is available to authorized users.

## Background

Three billion people rely on biomass fuels for their cooking and heating needs worldwide. Biomass fuels consist of dung, wood, charcoal, crop waste, etc. [1]. Combustion of these fuels leads to high levels of particulate matter, carbon monoxide, polycyclic aromatic hydrocarbons, and other deleterious air pollutants [2–6]. In this context, these air pollutants are collectively referred to as household air pollution (HAP). The health effects of HAP are vast and wide-ranging. In fact, it is estimated that 3.9 million premature deaths are attributable to HAP annually [3]. Deaths attributable to HAP occur from a diverse set of diseases such as stroke, ischemic heart disease, pneumonia, cataracts, etc. [3, 7]. Although disease etiology and causal mechanisms are outstanding, it is widely acknowledged that HAP is a severe health threat. Therefore, efforts are being made to characterize and mitigate exposure. This protocol paper outlines the Enhancing LPG Adoption in Ghana (ELAG) study, a cluster-randomized controlled trial designed to increase LPG stove adoption and sustained use.

### Mitigating HAP exposures

HAP exposures result from combustion of biomass and other solid fuels in traditional cookstoves [8]. Public health proponents have looked to cleaner cookstoves to reduce HAP exposures [9, 10]. However, a number of recent studies establish that clean cookstoves do not automatically reduce HAP exposures [11]. Stove stacking, wherein households partially adopt the new technology while maintaining use of traditional cooking technologies, is a core challenge [12–15]. While partial adoption of cleaner cookstoves may partially reduce exposure, prior work has shown that these reductions are not sufficient to eliminate risk [16]. Another challenge facing clean cookstove interventions is that community-level emissions may substantially contribute to individuals’ exposure [17, 18]. Therefore, large scale adoption of clean cooking technologies may be required to decrease overall HAP exposures. These challenges have led to a body of scientific literature dedicated to clean cookstove adoption that addresses the determinants of uptake of the new technologies [19–22]. Ultimately these studies seek to understand opportunities to intervene on HAP exposure. For our purposes, ‘improved cookstoves’ refer to those which still utilize biomass, but increase the efficiency of combustion and thereby reduce HAP exposures. ‘Clean cookstoves’ on the other hand, refers to non-biomass stoves, including liquefied petroleum gas (LPG), induction, solar, biogas, etc.

### Efficient cookstove adoption

The scientific literature regarding cookstove adoption has identified numerous pre-conditions often associated with adoption. These variables can be broadly divided into three categories: household/setting characteristics, infrastructure, and knowledge and perceptions [20–22]. Household/setting characteristics are features that describe the household, their neighbors, and/or communities. Examples include ethnicity, religion, maternal and paternal education, female head of household, parental and family wealth/income, household size, and age. While it is regularly true that these variables predict adoption, the direction of the association varies across studies [21]. The reasons behind these inconsistencies are unexplained, but may represent uncontrolled confounding based on underlying constructs that are contextually relevant, or they may indicate the central role of local conditions in shaping decision processes.

Access-related factors associated with cookstove adoption include 1) financial, tax, and subsidy aspects (2) market development (3) regulation, legislation, and standards, and (4) programmatic and policy mechanisms [20–22]. Broadly defined, the access factors outline contextual physical and/or organizational facilitators of clean cookstove adoption and sustained use. Fuel access factors are also oftentimes specific to the stove type. For example, improved biomass cookstoves necessitate a different fuel infrastructure than LPG stoves. After an initial stove purchase, some stoves require repeated purchase of fuels. Users are then responsive to the price of the physical stove, but also fuel prices. Considering the fuel access environment of cookstove adoption is imperative for HAP-related interventions.

Understanding knowledge and perceptions preventing behavior change is vital to any health-related intervention. Studies have shown numerous associations with cookstove adoption, including knowledge/perceptions of: the health impacts of HAP, safety benefits of new cookstoves, time-savings benefits, improved cleanliness of newer stoves, social norms, newer cookstove users within a social circle, and the cultural appropriateness of technologies [20, 21]. Generally speaking, knowledge is regarded as highly modifiable whereas attitudes can be more challenging to alter [23, 24]. Both elements, however, must be aligned with a new behavior in order to observe behavior change [25].

### Challenges in cookstove adoption research

Studying cookstove adoption is both conceptually and methodologically challenging. Disciplines involved span the social, environmental, and health sciences, utilizing quantitative, qualitative, and mixed methods [26–30]. The field has largely employed observational study designs to date. While these studies are quite informative, they may be vulnerable to selection bias because individuals opt into each group of the study by deciding whether or not to purchase a stove, sustain use, etc. There may be underlying characteristics that predict entry into each group, thus limiting the generalizability of findings. Controlled trials can address these limitations through the randomization and follow up of participants, but there are few studies utilizing these study designs [31, 32].

Most cookstove adoption studies have focused on initial adoption versus sustained use. [21, 33]. This is an important distinction because adoption studies have largely focused on the enablers and barriers of initial stove acquisition and/or the use of the technology early in its adoption [13]. However, there are many reasons to believe that behaviors change over time. For example, researchers have noted situations wherein new stove use is high upon acquisition, but decreases over time. There are plausible reasons why participants would decrease use. New stoves could break with consistent use, and without access or means of repair, participants would likely default to the traditional stove. It is also possible that a household’s financial circumstances change and use falters. Without clear plans to recover from these external stimuli, users would resume traditional stove use. While there is a small number of studies focused on sustained use, that amount is growing. This is because researchers increasingly recognize the importance and complexity of the issue [13, 34, 35].

Household/setting characteristics, infrastructure, and knowledge and perceptions are all highly contextual issues. Although adoption has been extensively studied around the world, much work remains. Sub-Saharan Africa has the largest proportion of individuals using biomass fuels for cooking, and is the only region globally where traditional biomass use is still growing [36]. Sustained use studies are small in number and limited geographically. To our knowledge, there have been few studies in sub-Saharan Africa, demonstrating a need for continued research in an important region.

The goal of this paper is to outline the study design for the ELAG Study. The objectives of ELAG is to assess the effectiveness of two interventions on facilitating sustained use of LPG. A cluster-randomized trial with a factorial design is being used to test the effectiveness of two distinct interventions: 1) a behavioral change intervention using the Risks, Attitudes, Norms, Abilities, and Self-Maintenance (RANAS) model and (2) an access intervention to modify the ease of refueling [37]. The factorial design also allows us to evaluate the interaction of these two interventions. We deliver these interventions to mothers and, when possible, their partners. Sustained use is measured with stove use monitors (SUMs). These monitors will be in place for 12 months after intervention delivery. Sustained use will be assessed by analyzing the effect of the interventions on stove use in the last 6 months of the study period. We believe that this study will offer novel insights into the predictors of sustained use, strategies that can be employed to increase use, and important policy actions that can reduce exposures to HAP and its health consequences.

## Methods/design

This study builds on an ongoing successful collaboration between Columbia University in the City of New York and the Kintampo Health Research Centre (KHRC). In fact, the study is an outgrowth of the Ghana Randomized Air Pollution and Health Study (GRAPHS), which was a 5-year cluster-randomized controlled trial assessing the impacts of a HAP intervention on low birthweight and pneumonia [38]. GRAPHS included one control, and two intervention arms. LPG stove users and improved cookstove (Biolite) users served as the interventions and the traditional 3-stone fire users were the control arm. Ethical considerations dictated that the control arm would receive clean cookstoves upon study completion since LPG stoves are believed to reduce HAP exposures the most substantially. Given remaining resources upon study completion, all participants in the control and Biolite arms were scheduled to receive LPG stoves at study closeout. This provided an opportunity to assess patterns of adoption and sustained use of LPG cookstoves among a large group of participants.

### Hypothesis

We hypothesize that households that receive both the behavioral and access interventions will demonstrate higher levels of sustained use in the last 6-months of the study period, compared to those in the no intervention group, see Table 1.

**Table 1 Tab1:** Allocation of clusters by study arm (and number of households)

	No educational intervention	Educational Intervention	Totals
	No. of communities *(households)*	No. of communities *(households)*	
No agent delivery	7 (271)	7 (243)	14 (514)
Agent delivery	7 (241)	6 (224)	13 (465)
Totals	13 (492)	12 (451)	27 (979)

### Study setting

The study area is in Kintampo North Municipality and Kintampo South District in the Brong-Ahafo Region of Ghana. This is a mostly rural area (population 176,480), see Fig. 1 [39]. Households in the study area traditionally use three-stone fires for their cooking needs. Ghana has a warm climate, with an annual average temperature is 26 °C [40]. Therefore, stoves are typically only used for cooking, not heating. There are two seasons, wet and dry. During the dry season most cooking takes place outdoors while enclosed or covered kitchen areas are the site of most cooking in the wet season. Wood is the main fuel source in the study area, but charcoal is used as well [41].

**Fig. 1 Fig1:**
[figure not shown]
Map of Kintampo, the study area

### Study eligibility & recruitment

ELAG participants are limited to participants who were enrolled in the original GRAPHS cohort and who: 1) were originally randomized to the Biolite or control arms of the study and 2) still reside in the KHRC study region (see Fig. 1). Participants are visited to assess interest in the new study, although, due to longstanding involvement with GRAPHS and other KHRC initiatives, we do not anticipate any issues reaching our recruitment goals.

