### Randomization

The parent study utilized a cluster-randomized design on coarsened exact matches to assign study treatments [54]. This study re-randomized clusters employing a covariate-constrained randomization approach with several identified prognostic covariates [55, 56]. The covariate-constrained randomization approach is a powerful allocation technique to ensure balance between arms in cluster randomized trials. Baseline covariates were chosen based on prior literature and theoretical relationships (see Table 2). When covariates are continuous, balance is determined via mean differences between treatment arms. Maximum permissible imbalance is designated a priori. Given these parameters, allocation amongst arms is randomly designated if below the maximum permissible imbalance. An independent epidemiologist performed the final randomization using the *ccrand* procedure in Stata [57]. Allocation was not revealed to field staff until after baseline data collection was complete.

**Table 2 Tab2:** Covariate constrained randomization variables

Variable	Rationale
Community Asset Index	Scientific articles have shown that differential access to resources can be predictive in the uptake of new cookstove technologies (19–21).
Average Household Size	Scientific articles have shown that household size can be predictive in the uptake of new cookstove technologies (19–21).
Distance to Refueling Station	Study communities are scattered throughout the region at varying distances from the refueling center. Further distances are likely a deterrent to refuel for non-Agent delivery households, *see map*.
Households per cluster	To ensure roughly equal number of participating households per arm.

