### Analysis

The primary analysis will be to examine the effect of the intervention on average stove use over the final 6 months of the observation period. Due to the nested nature of the observations, these data will be analyzed with a hierarchical linear model. The three intervention arms, consisting of the two interventions alone and one combined, will be compared to the control arm, which receives no intervention.

Several secondary analyses are also of interest. First, while the primary analysis is unadjusted for potential covariates, a secondary analysis will include covariates such as financial literacy, the number of unanticipated life events necessitating additional financial resources, ethnicity, intra-household cooperation, and household asset index. Second, additional analyses will look at the various trends across time, assessing stove use in the first 5 months of the study and over the 10 months. A third analysis will analyze sustained use across arms by demographic characteristics identified in improved cookstove adoption related systematic reviews. Finally, given that the Ghanaian government is already distributing LPG cookstoves and interested in increasing sustained use, this research is policy-relevant. Qualitative data will be collected and analyzed among key stakeholders involved in the intervention. This analysis can then be used to consider meaningful ways to scale the intervention based on existing fuel infrastructure.

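### Parent-trial stove arm, a known and plausibly prognostic community-level factor, is neither a randomization constraint nor a term in the stated primary model; adding it is a cheap gain in precision and protects against chance imbalance

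*Protocol article*

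**What the plan says.** The protocol article restricts eligibility (Study eligibility & recruitment) to people who "were originally randomized to the Biolite or control arms of the study" and who still live in the study region. Methods/design gives the stove history of those arms: "LPG stove users and improved cookstove (Biolite) users served as the interventions and the traditional 3-stone fire users were the control arm". Both groups then move to the same stove, since "all participants in the control and Biolite arms were scheduled to receive LPG stoves at study closeout".

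The Randomization section says of the parent trial: "The parent study utilized a cluster-randomized design on coarsened exact matches to assign study treatments". Parent-trial arm is therefore essentially a community attribute. For ELAG itself: "This study re-randomized clusters employing a covariate-constrained randomization approach with several identified prognostic covariates". Table 2 lists four such covariates, each with a rationale: community asset index, average household size, distance to the refueling station and households per cluster. Parent-trial arm is not one of them.

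The Analysis section states: "while the primary analysis is unadjusted for potential covariates, a secondary analysis will include covariates such as financial literacy". The other covariates it names are unanticipated life events, ethnicity, intra-household cooperation and household asset index. Parent-trial arm is not named, and no section discusses carry-over from the parent trial.

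**The concern.** A household's past with a study stove could affect how it uses the next one. The Background treats partial adoption alongside existing stoves as a central problem, and notes that use of a new stove can start high and then fade. Previous assignment to an improved stove is thus a plausible predictor of LPG minutes by the protocol's own reasoning, and it was on record before communities were allocated.

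With only six or seven communities per arm, a factor left to chance can end up unevenly spread. If it matters, the estimated contrast in this one trial carries part of its effect. Even when it is evenly spread, leaving it out of the model keeps its variance in the between-community error and widens the intervals.

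**Working it through.** **Inputs from the article**
- Communities per arm: 7, 7, 7 and 6 (cells of Table 1). The cells give 7 + 7 + 7 + 6 = 27 communities and 271 + 243 + 241 + 224 = 979 households, matching the Power section. The column totals printed in Table 1 do not match the cells, so the cells are used.
- SD of the outcome: 1000 min (Power). Effect sizes considered: 0.3 and 0.5 (Fig. 2 caption), that is 300 and 500 min.
- Contrasts: each of three intervention arms against control (Analysis).

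The article's own power values stand only in a figure that is not shown, and no ICC is given in the text, so they cannot be reproduced.

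**Assumptions not in the article**
- Number of ex-Biolite communities B: 9 to 18 of 27.
- Effect of stove history on LPG use, g: 0 to 0.5 SD.
- ICC: 0.05 and 0.10. Tests are two-sided at 5%.
- Allocation is simple random. The Table 2 constraint could not be imitated because no community data are given.

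**Step 1: expected imbalance.** Allocation is unrelated to parent-trial arm, so the expected difference in ex-Biolite share between any two arms is 0.

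**Step 2: spread of the imbalance.** For combined (6) versus control (7), with p = B/27:

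SD = √[ p(1 − p) × (27/26) × (1/7 + 1/6) ]

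- B = 13: √(0.2497 × 1.0385 × 0.3095) = 0.283
- B = 9 or 18: √(0.2222 × 1.0385 × 0.3095) = 0.267

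**Step 3: probability of a gap of at least 40 points** (random allocations)
- Combined versus control: about 0.15 across the range.
- At least one of the three contrasts with control: 0.36 (B = 9 or 18) to 0.41 (B = 13 or 14).

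**Step 4: what such a gap would do.** Three communities in seven is 3/7 = 0.43. Shift = 0.43 × g × 1000 min:
- g = 0.2: 86 min
- g = 0.3: 129 min
- g = 0.5: 214 min

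**Step 5: repeated-sampling behaviour and power.** Simulated community means (979/27 = 36.3 households each, 13 ex-Biolite), analysed by a linear model on arm with and without a parent-trial term. Power is for combined versus control at d = 0.5.

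| g (SD) | ICC | Unadjusted | Adjusted |
|---|---|---|---|
| 0 | 0.05 | 0.88 | 0.85 |
| 0 | 0.10 | 0.68 | 0.66 |
| 0.2 | 0.05 | 0.83 | 0.86 |
| 0.2 | 0.10 | 0.63 | 0.64 |
| 0.3 | 0.05 | 0.77 | 0.86 |
| 0.3 | 0.10 | 0.61 | 0.66 |
| 0.5 | 0.05 | 0.63 | 0.86 |
| 0.5 | 0.10 | 0.50 | 0.67 |

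The mean bias of the unadjusted contrast was at most 0.005 SD. Type I error was 0.049-0.053 unadjusted and about 0.05 adjusted. Adjusting gains about 1 to 23 points when g is 0.2-0.5 and loses about 2 when g is 0; simulation error is about a point.

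In this set-up the stove-history variance comes on top of the ICC. With about half the communities ex-Biolite it is g²/4: 0.01 at g = 0.2, and 0.0625 at g = 0.5, which exceeds an ICC of 0.05. The large gains belong to that upper end.

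**The case against.** A reader might infer that the arm contrasts are confounded with stove history. The article does not support that. Communities were re-randomized and nothing ties the new allocation to the old one. Step 5 shows no bias over repeated allocations and a type I error near 5%. The hierarchical model also carries unexplained variation between communities into its standard errors. The 86-214 min in Step 4 is a deviation conditional on an uneven allocation, in either direction.

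A reader might also infer that there was no washout, or that ex-Biolite households still own a working Biolite stove. Neither is stated: the article gives no interval between the two trials' stove use and does not say what became of the Biolite stoves. One parent-trial arm per ELAG community is likewise an inference from cluster randomization, because eligibility is worded per participant.

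The size is open to challenge too. No source in the article gives a carry-over effect, and 0.3-0.5 SD would equal a whole planned intervention effect. At 0.2 SD the power gain is only 1 to 3 points. The stated hypothesis concerns combined versus control, for which the relevant probability is about 15%, not 36-41%.

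Lastly, the article condenses a fuller plan, and its list of secondary covariates is introduced as examples. That stands for the secondary model, where adjustment may already be intended. It does not reach Table 2, which is presented as the list of constraint variables, or the statement "while the primary analysis is unadjusted for potential covariates".

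**Conclusion.** The point holds as a cheap improvement, not as a flaw that invalidates the comparison. A plausibly prognostic factor known before allocation was left out of the constraint set and out of the stated primary model. Validity over repeated randomization is intact. The exposure is to an uneven spread in the allocation actually drawn, and to avoidable loss of precision.

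The size depends on the count of ex-Biolite communities, the effect of stove history and the ICC, none of which the article gives, and on ignoring the Table 2 constraint. The actual imbalance is a fixed fact that the study team can read off its allocation list; it may be small.

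**What to change.** Add parent-trial arm (Biolite or three-stone fire) as a fixed covariate in the hierarchical linear model for the primary comparison. If the primary analysis is to stay unadjusted, prespecify an analysis adjusted for parent-trial arm and report it beside the unadjusted result. In either case, give the number of ex-Biolite communities and households per ELAG arm in the baseline table.

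The cost is one community-level degree of freedom and about 2 points of power if stove history proves irrelevant. No new data and no change to the completed randomization are needed. A display of intervention effects by parent-trial arm is not recommended: 27 communities over eight cells leaves about three per cell (27/8 = 3.4), too few to be informative.
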